# The feasibility and acceptability of conducting a randomised controlled trial evaluating a healthcare professional-supported, self-management intervention for people suffering from fatigue after critical illness

**DOI:** 10.1186/s40814-026-01798-7

**Published:** 2026-03-14

**Keywords:** Critical illness, Intensive care unit, Fatigue, Self-management, Feasibility

## Abstract

**Background:**

Fatigue is a common problem that significantly affects intensive care unit (ICU) survivors’ physical, psychological, and social functioning. ICU survivors often experience a loss of self-worth and identity, struggle to return to their normal roles, and face ongoing challenges with cognitive and emotional recovery. Despite its profound impact, there are limited rehabilitation interventions targeting this population. This research aims to evaluate the acceptability of implementing the Fatigue After CriTical illness (FACT) self-management intervention into usual care for patients experiencing fatigue after critical illness and the feasibility of the intervention for a future clinical trial.

**Methods:**

This is a multicentre, open-label, feasibility randomised controlled trial (RCT) with an embedded qualitative evaluation, conducted across. Seventy participants recruited from three United Kingdom (UK) National Health Service (NHS) Trusts will be randomised either to the FACT self-management intervention following hospital discharge, which focuses on fatigue management, goal setting, and personal action planning, in addition to usual care, or to a control group receiving usual care alone. The intervention will be accessible for six months and will include a 30-min phone or video call with an ICU follow-up healthcare professional (HCP) in the third month. HCPs will attend an online training session and follow a protocol to guide patients in goal setting. Outcome assessments will occur at baseline, three months, and six months post-randomisation to evaluate feasibility and acceptability. Semi-structured interviews with patients and HCPs will explore their experiences and acceptability outcomes at 6 months.

**Discussion:**

This study aims to provide insights into the feasibility and acceptability of the FACT intervention, with the goal of improving fatigue management among survivors of critical illness. Preliminary findings will inform the design of a larger-scale RCT to evaluate its effectiveness in enhancing recovery from critical illness in patients who are experiencing fatigue.

**Trial registration:**

Study ID: ISRCTN1381359. Date registered: 01/04/2025.

**Supplementary Information:**

The online version contains supplementary material available at 10.1186/s40814-026-01798-7.

## Background

Fatigue is a distressing and debilitating symptom experienced by people who are recovering from critical illness and is described as an overwhelming mental and physical exhaustion [1, 2, 29]. As highlighted in the context of post-intensive care syndrome, intensive care unit (ICU) survivors, similar to many other patient populations, often face clusters of symptoms rather than isolated impairments. These symptoms affect multiple functional domains [8] and lead to diminished mental and physical capacities, impacting various aspects of daily life [1, 8]. This can include a loss of identity and self-esteem, sleep disturbances, and cognitive fatigue, which negatively influence concentration, thought processes, and memory [12, 17]. Fatigue has a detrimental impact on physical and psychological well-being and health-related quality of life (HRQoL) in people recovering from critical illness, and is one of the three most significant problems described by people recovering from critical illness, along with a lack of physical strength and decreased walking distance [28]. Our systematic review found that up to 81% of people report symptoms of fatigue 4 months after ICU discharge, with 50% (equating to 82,000 per year in the UK) reporting persistent fatigue at 1 year [2]. 

People recovering from critical illness often rely heavily on the support of others and may be unable to carry out their usual family, social, and work roles, leading to reduced self-worth or a loss of identity [1, 2]. This can be compounded by a lack of understanding and empathy from healthcare professionals (HCPs), employers, and family members [1, 2, 26]. People who have experienced critical illness often report requiring assistance with activities of daily living (ADLs) (e.g. toileting, hygiene) many months after hospital discharge [1, 34]. People in the first year after ICU discharge also have multiple encounters with primary care physicians [25] and Schmidt et al. [33] found that many require long-term aftercare. Helping people manage their fatigue after critical illness has the potential to increase engagement with rehabilitation, improve physical performance, promote social (re)integration, and improve overall HRQoL.

Despite its prevalence, fatigue remains under-recognised in the current literature. Our systematic review found that there were no existing interventions to support rehabilitation specifically for people with fatigue after critical illness [2]. However, our umbrella review of self-management interventions for fatigue secondary to any acute or long-term condition found that these interventions had positive effects on patients, particularly when supported by HCPs [6]. Survivors require skill-building, interprofessional support, and tailored strategies to break the cycle of fatigue and inactivity [18, 20].

Although definitions of self-management vary, it generally refers to self-directed activities, where people take a leading role in managing their symptoms. The primary goal is often to improve coping and illness management, rather than achieving objective symptom improvement—though this may also occur [6]. Common self-management activities include accessing educational materials, symptom tracking, goal setting, and monitoring progress [14, 24]. Goal setting has proven effective in self-management strategies for energy conservation treatment [3] as it helps people to organise themselves in a way that maximises engagement while minimising energy depletion [20].

To address the need for targeted rehabilitation, we co-produced, with ICU survivors and carers, a theory-based, HCP-supported self-management intervention for fatigue after critical illness, known as FACT (managing Fatigue After CriTical illness), and tested it with service users. Three workshops were conducted with people experiencing fatigue after critical illness, along with family members and HCPs, to co-develop the first draft of the FACT intervention, which was subsequently designed in online and electronic formats. User testing (*n* = 4) found that the intervention was well received. Participants valued the intervention, reporting that it helped them to manage their fatigue and prioritise daily activities [7].

## Aims and objectives

This study aims to determine the feasibility and acceptability of conducting a randomised controlled trial (RCT) of the FACT intervention. The objectives are:Primary objective: To assess the willingness of people affected by fatigue after critical illness to participate in an RCT evaluating an HCP-supported self-management intervention for fatigue after critical illness.Secondary objectives:To estimate recruitment, retention, and the variability of outcome measures to inform sample size calculations and choice of outcome measures for a future effectiveness trial.To evaluate the acceptability and fidelity of the intervention by assessing adherence, estimated frequency of visiting the website, and patterns of use.To evaluate HCPs’ perceptions and experiences of delivering support for this intervention.

## Materials and methods

The study protocol is reported using the Standard Protocol Items: Recommendations for Interventions (SPIRIT) statement guidelines [10, 11] and the publication associated with the trial’s findings will be reported in accordance with the CONSORT extension for randomised pilot and feasibility trials [16]. A SPIRIT checklist is provided in Additional file 1.

### Study design

The study is a multicentre, open-label, feasibility RCT, with a qualitative evaluation of acceptability, conducted across ICUs at three UK NHS Trusts. A total of 70 participants will be randomised in a 1:1 ratio by sealed envelopes to receive the FACT intervention in addition to usual care or usual care alone. The intervention will be made available to the patients on hospital discharge and be accessible for 6 months. Participants will have a 30-min supportive phone/video call with an HCP from the ICU follow-up team at each site for three months. HCPs will attend an online training event and follow a defined protocol to facilitate goal-setting and personal action-planning. This study is an open-label trial; therefore, there will be no blinding to the participants or the trial management team.

All participating research sites offer inpatient ICU follow-up services. Patients who were in the ICU for more than 72 h are offered outpatient services at three months after hospital discharge, where physical and psychological health outcomes are evaluated. Where necessary, appropriate referrals and treatment plans are made. In the control group, patients (*n* = 35) will receive standard care, which includes routine follow-up services at their respective sites. Standard care typically involves a review of the patient’s recovery status without any additional interventions provided by the study. Additionally, patients may access generic information about recovery after critical illness, which is available on a variety of websites, including resources addressing fatigue. A flow chart of the study is presented in Fig. 1.

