### Recruitment

This study will recruit patients from ICUs from three NHS Trusts: Oxford University Hospital Foundation Trust (OUHFT), Guy’s and St. Thomas’ NHS Foundation Trust (GSTT), and University Hospitals Coventry and Warwickshire NHS Trust (UHCWT). These trusts cover geographically diverse patient populations, including a range of case complexity, ethnic backgrounds, and levels of social deprivation.

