### Data management

All study data will be entered into REDCap, a secure, validated electronic data capture system. REDCap ensures data accuracy and integrity through a range of built-in checks, automated error detection, and logging of data modifications. The system is programmed to only allow data entries within predefined value ranges, minimising the potential for errors. Participants will be identified within REDCap by a unique, trial-specific identification code. To ensure data quality, regular data audits will be conducted by the Trial Management Group to identify and correct inconsistencies. Staff responsible for data entry will undergo training to standardise procedures and minimise errors. These procedures adhere to Good Clinical Practice (GCP) standards and ensure the reliability of all data collected during the study.

No identifying personal information will be stored alongside the trial data to ensure participant confidentiality. Participants will be allocated a trial-specific identification code and will only be referred to by the code on all research documentation. For paper-based questionnaires returned to the Trial Management Group (TMG), the data will be manually entered into REDCap by research staff. During the study, all electronic data will be securely stored in REDCap. The Google Drive folder will be double password protected and accessible only to authorised members of the research team. Paper copies of questionnaires and informed consent forms will be stored in a locked filing cabinet in a secured office at Oxford Brookes University. Audio recordings of participant interviews will be downloaded immediately after recording and saved as MP3/MP4 files on the Oxford Brookes Google Drive along with the transcriptions of these interviews. Once transcripts have been checked for accuracy, the recordings will be deleted from the recording devices and Google Drive. At the end of the study, all research data will be archived on the Oxford Brookes approved long-term data repository, Arkivum. This data set will not be opened, and data will be stored for a period of 10 years, after which it will be automatically deleted.

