#### Primary outcome measures

The primary outcome focuses on the willingness of people affected by fatigue after critical illness to participate in an RCT evaluating an HCP-supported, self-management intervention. Recruitment and retention rates are critical indicators.

Recruitment rate is defined as the number of participants recruited or randomised as a proportion of those eligible and approached. This rate will be assessed at baseline and calculated both overall and by the research site.

Retention rate is defined as the proportion of participants who complete all the required questionnaires and semi-structured interviews. This outcome is essential to evaluate participant engagement and the feasibility of collecting follow-up data.

Assessments will be completed via phone or video call at baseline, three months, and six months post-randomisation. During the baseline data collection phase, additional demographic information (including age, sex, ethnicity, employment status, and marital status) and medical history (including comorbidities, primary diagnosis on ICU admission, ICU length of stay, hospital length of stay, days of mechanical ventilation, and severity of illness assessed by the APACHE III [22] will also be collected.

The progression criteria for full trial are summarised in Table 1.

**Table 1 Tab1:** Progression criteria

Category	Recruitment	Retention and follow-up completion	Remedial action
Green (Go)	> 85% anticipated (> 60 participants)	At least 80% of survivors will provide complete follow-up data	Continue—no action needed. Apply for further funding
Amber (Amend)	50–85% anticipated (36–75 participants)	60–80% of survivors will provide complete follow-up data	Continue—action needed. Explore ways to improve recruitment/retention
Red (Stop)	< 50% anticipated (< 35 participants)	< 60% of survivors will complete follow-up data	Stop. Explore reasons for poor recruitment/retention

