### Administrative structures

The study will be monitored by the TMG, which includes the Chief Investigator, Principal Investigators (PIs), patient co-applicant, research team, and the trials unit team. The TMG will meet biweekly during the planning and set-up phases of the trial and every four weeks during the trial’s operational phase. The TMG will ensure adherence to agreed milestones and provide rapid responses to any issues that arise.

In addition to the TMG, the PAG and Clinical Advisory Group (CAG) will provide additional support to the trial. The PAG, chaired by patient co-applicants and supported by PPIE lead researchers and other patient and carer representatives, will meet every two months. Their role will include advising on recruitment materials, reviewing study outputs, contributing to dissemination plans, and supporting the documentation of the study’s impact. The CAG, composed of HCPs who work with patients recovering from critical illness, will meet quarterly to offer input on recruitment strategies, monitor study progress, and guide analysis, dissemination, and implementation processes.

These structured oversight mechanisms will ensure the trial’s progress is carefully monitored, with input from diverse stakeholders, including researchers, clinicians, and patient representatives.

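### Sealed envelopes are the only stated allocation method in an open-label, three-site trial; central release after registration would be a safer choice at small cost, though no bias is shown

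*Protocol article*

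**What the plan says.** Under Study design the protocol article states that the 70 participants are to be "randomised in a 1:1 ratio by sealed envelopes". No other allocation method appears anywhere in the article. The same section states: "This study is an open-label trial; therefore, there will be no blinding to the participants or the trial management team". The Recruitment section adds: "This study will recruit patients from ICUs from three NHS Trusts".

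Under Primary outcome measures, the first feasibility outcome is set out as follows: "Recruitment rate is defined as the number of participants recruited or randomised as a proportion of those eligible and approached". The Secondary outcome measures and Data analysis sections also plan an exploratory comparison of questionnaire results between the arms.

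Two other places bear on what could replace envelopes. Data management says: "All study data will be entered into REDCap, a secure, validated electronic data capture system". Administrative structures includes in the Trial Management Group the "research team, and the trials unit team".

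**The concern.** Concealment protects the step between judging a patient suitable and learning the arm. With envelopes, that protection depends on how they are made, numbered and held. With central release, the allocation is not issued until the patient has been irrevocably registered.

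Several features of this trial make the step worth protecting. Arms are not blinded, so earlier allocations can become known. The Intervention section describes one manual that takes research delivery nurses from screening through to follow-up, so the same role may span approach and later contact. Entry involves some judgement: ability to comply, the clinical team's view of expected survival, and a window of seven days either side of discharge. Someone who knew or guessed the next allocation could defer a patient or not approach one.

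Two things would be at stake. The first is the comparability of the arms, and with it the exploratory comparison. The second is the approached-based recruitment rate, because a patient who is left unapproached drops out of its denominator.

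**Working it through.** The article gives no figure on allocation or concealment, so there is none of its own to reproduce. The one arithmetic check available is arm size: 70 / 2 = 35 per arm, which agrees with "In the control group, patients (*n* = 35) will receive standard care".

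**What the article settles and what it leaves open**

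- Settled: envelopes, 1:1, open label, three Trusts, and a recruitment rate whose denominator is patients eligible and approached.
- Not stated: whether envelopes are opaque or sequentially numbered, who prepares and holds them, where they are kept, and how the sequence is generated. A condensed article commonly leaves such details to the full protocol, so their absence is not counted against the plan.
- Not stated: whether the data system or the trials unit team can issue allocations.

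**Illustration 1: recruitment rate.** All inputs are assumptions; none is in the article. Let E be the eligible patients, p the true uptake, f the share of allocations foreseen, and s the share of likely decliners left unapproached when the foreseen arm is unwanted, taken to be half the time.

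Removed from the denominator = E × (1 − p) × f × 0.5 × s

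Observed rate = E × p / (E − removed)

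With E = 1000:

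| p | f | s | Removed | Observed rate | Shift (percentage points) |
|---|---|---|---|---|---|
| 0.5 | 0.05 | 0.5 | 6.25 | 500 / 993.75 = 50.3% | 0.3 |
| 0.5 | 0.25 | 1 | 62.5 | 500 / 937.5 = 53.3% | 3.3 |
| 0.4 | 0.25 | 1 | 75 | 400 / 925 = 43.2% | 3.2 |
| 0.6 | 0.25 | 1 | 50 | 600 / 950 = 63.2% | 3.2 |

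Over p from 0.4 to 0.6, f from 0.05 to 0.25 and s from 0.5 to 1, the shift runs from about 0.3 to 3.3 points.

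**Illustration 2: arm comparability.** Again by assumption, let a share f of allocations be steered, with a prognostic difference of d SD between the patients steered to each arm.

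Expected baseline difference = f × d

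- Low: 0.05 × 0.5 = 0.025 SD
- High: 0.25 × 1.0 = 0.25 SD
- Chance standard error at 35 per arm: √(2/35) = 0.239 SD

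At the low end the effect is lost in chance variation. At the high end it is about one standard error.

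These ranges show what foreknowledge could do if it occurred to the assumed extent. They do not estimate how often it would occur with this trial's envelopes.

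**The case against.** The strongest reply is that sealed envelopes are an accepted method. If they are opaque, sequentially numbered and independently held, they can conceal allocation. The article does not say that recruiting staff hold them. The Study setting section has a university team coordinating the study, so central custody is not excluded. This stands, and it is why the point cannot be put as an error.

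The consequences are also limited. The recruitment criterion in Table 1 is tied to participant counts, which are less exposed to selective approach than the proportion. The Data analysis section already calls its inferences tentative. Both points stand, although the proportion remains part of the primary outcome.

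A reader might make four stronger inferences, which the document does not support.

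- **That central allocation is already available at no extra effort.** REDCap is described for data capture only, and the trials unit team appears as a member of the management group with no stated allocation role. Site access to REDCap is not described either.
- **That staff can open or reorder envelopes.** Custody is simply not described.
- **That predictability of blocks, or chance imbalance within sites, measures the problem.** The article states neither a block size nor simple randomisation. Both are properties of the sequence, and central release alone would not change them.
- **That the definitive trial's allocation procedure goes untested.** The article does not say what that procedure will be, and testing it is not among the objectives.

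What survives is that the article names a method, and that a generally preferred one exists. That is a comment on a stated choice, not on a missing detail.

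**Conclusion.** The point holds as a cheap improvement, not as a demonstrated flaw. Bias is possible and not shown, and its size cannot be derived from the article. The illustrative shift in the recruitment rate and the illustrative baseline difference rest wholly on assumed shares of foreseen or steered allocations, assumed uptake and an assumed prognostic difference. No figure stated in the article changes. The conclusion rests on three stated facts: envelopes as the sole method, no blinding, and a primary rate that depends on who is approached.

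**What to change.** In Study design, replace the reference to sealed envelopes with central allocation through the trial's electronic data system or the trials unit team, after confirming that one of them can randomise. Release each allocation only once eligibility, consent and baseline data are recorded. Stratify by site and use varying block sizes that are not disclosed to recruiting staff; this is needed because central release does not by itself make a sequence unpredictable.

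The cost is a short set-up and an amendment. The downside is that sites need online or telephone access at the moment of randomisation. If neither system can randomise, set-up would take more, and stating the envelope safeguards is the proportionate alternative.

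Timing matters. The Intervention section expects recruitment to be complete by the end of 2025, and the article was published in March 2026. If recruitment is still open, the change can apply to the remaining participants. If it is finished, the trial report should describe who held the envelopes, give the results of checks of envelope order against the sequence, and state the concealment limitation. That costs almost nothing.
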